#### Clinical outcomes

Clinical outcomes will be the following: (1) metabolic responses, will be evaluated by metalyzer device and blood sampling and (2) arterial stiffness, will be evaluated by sphygmocor device.

#### Feasibility outcomes

The feasibility of recruitment will be determined by calculating the proportion of enrolled participants from those screened for eligibility from the varied recruitment sources. Retention will be measured by the percentage of participants completing the study through the post-assessment. Intervention adherence will be measured from the information recorded by a nutritionist at three test days. The study will be deemed successful if (1) 60% recruitment target is achieved, (2) 80% or more of the subjects completed this study, and (3) subjects and investigators report acceptability of the study and adherence to the sample collection protocol will be reviewed by investigators.

## Statistical analysis

Briefly, descriptive statistics will be used to summarize enrollment adherence, recruitment rates, and dropout. Feasibility outcomes will be presented as percentage and 95% confidence intervals. A retention rate of > 80% will be considered as feasible to conduct a future RCT. Analysis of outcomes will be conducted using both intention to treat. Also, in the analysis of clinical outcomes, descriptive statistics will be used to compare and determine the primary characteristics of the study groups, and the normal distribution of the variables will be evaluated using the Kolmogorov-Smirnov test. In total, 24 subjects have been assigned to the obese and normal groups. The baseline comparisons between the groups will be performed using the independent samples *t* test or Mann-Whitney *U* as appropriate. In addition, repeated-measures analysis of variance (ANOVA) will be used to assess the timing effect of the research parameters in various phases of the study. Data will be used for sample size estimation and to determine the most appropriate outcome measure for the main study.

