### Participants and data collection

Data collection will be performed by two nutritionists and one nurse, who have been trained on the proper use of various devices and are able to complete the questionnaires accurately. Since this is a pilot study, we cannot assess the attrition rate, and it is also not necessary to define and calculate the sample size. Our study follows sample size for pilot trial and aims to have at least 12 subjects per group who provide full data( in total 24 subjects) [31]. This sample size will to provide a pooled standard deviation that provides enough precision for the development of a future study.

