#### Outcomes

The primary outcome will to evaluate the feasibility of conducting a trial to compare the effect of three test meals in lean and obese men. The feasibility will be assessed by measuring subject compliance with the intake of three test meals, recruitment, and retention rate in 3 days of study. Also, adherence to sample collection protocol will be assessed. Secondary outcomes will to compare the effect of three test meals on metabolic responses and vascular parameters in lean and obese men for sample size calculation.

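### The pilot's primary feasibility decision is stated inconsistently: three joint criteria under Feasibility outcomes, but a retention threshold with no other criterion mentioned in the Statistical analysis section

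*Protocol article*

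**What the plan says.** The Outcomes section of the protocol article sets the primary outcome: "The primary outcome will to evaluate the feasibility of conducting a trial to compare the effect of three test meals in lean and obese men". It lists several components: "The feasibility will be assessed by measuring subject compliance with the intake of three test meals, recruitment, and retention rate in 3 days of study". Adherence to the sample collection protocol is added in the next sentence.

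The Feasibility outcomes section defines recruitment by "calculating the proportion of enrolled participants from those screened for eligibility" and says "Retention will be measured by the percentage of participants completing the study through the post-assessment". It then gives a joint rule: "The study will be deemed successful if (1) 60% recruitment target is achieved, (2) 80% or more of the subjects completed this study, and (3"; the third condition is that "subjects and investigators report acceptability of the study and adherence to the sample collection protocol will be reviewed by investigators".

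The Statistical analysis section summarises the feasibility measures descriptively, with percentages and 95% confidence intervals, and then states: "A retention rate of > 80% will be considered as feasible to conduct a future RCT". It attaches no decision to recruitment, acceptability or adherence, and it does not refer back to the joint rule.

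Two other places bear on the point. Participants and data collection "aims to have at least 12 subjects per group who provide full data( in total 24 subjects". The Conclusion makes the design of a larger study depend on a significant result among the measured parameters.

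**The concern.** The pilot exists to decide whether a larger trial should follow, so the rule for that decision is its main pre-specified element. Two sections state it differently, and no text says which applies or that the second covers only one component of the first.

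Retention is measured among men already enrolled, so a retention threshold cannot register poor recruitment. Nor can it register an unfavourable report on acceptability. If the rule is left unresolved, the choice between the two statements could be made after the results are known. The difference runs mainly towards the favourable verdict: the Statistical analysis sentence can be met when the joint rule is not.

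**Working it through.** The document gives no power or sample size calculation to reproduce, so the check compares the two rules directly.

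**1. The rules side by side**

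| Criterion | Feasibility outcomes | Statistical analysis |
|---|---|---|
| Recruitment | 60% target required | not mentioned in the verdict |
| Retention | ≥ 80% | > 80% |
| Acceptability | required (no numerical cut) | not mentioned in the verdict |
| Conclusion drawn | study successful | future RCT feasible |

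**2. An example that splits them**

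Take 60 screened, 24 enrolled and 22 completing. Recruitment is 24/60 = 40%, and retention is 22/24 = 91.7%. The Statistical analysis sentence gives feasible. The joint rule gives not successful, if the 60% target means enrolled over screened. Good retention with unfavourable acceptability splits the rules in the same way, whatever the target means.

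**3. How often they could disagree over recruitment**

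Inputs from the protocol: 24 men, an 80% retention cut and a 60% recruitment cut. Assumptions, which are not in the protocol:
- recruitment stops at 24 enrolled;
- the 60% target is enrolled over screened;
- recruitment and retention are independent;
- acceptability is met;
- the true rates are as shown in the table.

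Retention passes with at least 20 of 24 completers (0.80 × 24 = 19.2). For X ~ Binomial(24, p), P(X ≥ 20) = 0.460, 0.713, 0.915 and 0.994 at p = 0.80, 0.85, 0.90 and 0.95.

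Recruitment passes if 24 men are enrolled within 24/0.60 = 40 screened. For Y ~ Binomial(40, q), P(Y ≥ 24) = 0.134, 0.568 and 0.937 at q = 0.50, 0.60 and 0.70.

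P(disagree) = P(X ≥ 20) × [1 − P(Y ≥ 24)]. For p = 0.90 and q = 0.50 this is 0.915 × (1 − 0.134) = 0.79.

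| True retention | Recruitment 50% | 60% | 70% |
|---|---|---|---|
| 80% | 0.40 | 0.20 | 0.03 |
| 85% | 0.62 | 0.31 | 0.05 |
| 90% | 0.79 | 0.40 | 0.06 |
| 95% | 0.86 | 0.43 | 0.06 |

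**4. The other reading of the 60% target**

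If the target means 60% of the 24 planned men, it needs 0.60 × 24 = 14.4, that is 15 enrolled. A study that reaches 24 then meets it at 100%, and recruitment cannot split the rules. They split only if enrolment stops short. For example, 14 enrolled (14/24 = 58.3%) with 12 completing (12/14 = 85.7%) fails the joint rule and passes the retention sentence.

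**5. The inequality signs**

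| Enrolled | Completers for ≥ 80% | Completers for > 80% |
|---|---|---|
| 24 | 20 | 20 |
| 25 | 20 | 21 |
| 26 to 29 | 21 to 24 | the same |
| 30 | 24 | 25 |

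With 24 enrolled, 19/24 = 79.2% and 20/24 = 83.3%, so the signs agree. With 30 enrolled and the planned 24 completers, retention is exactly 80%. That meets criterion (2) of the joint rule and misses the Statistical analysis threshold, so here the conflict runs the other way.

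**The case against.** The strongest defence is that the Statistical analysis sentence is a loose restatement of criterion (2). It uses the same 80% figure, sits in a paragraph offered as a brief summary, and follows sentences that cover the other feasibility measures. It does not say that retention is the only condition. That reading is plausible and may be what was intended. It does not remove the problem, because the sentence names the overall conclusion about a future trial, not the adequacy of retention, and nothing confines it to one component.

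A second defence is that a successful study and a feasible future trial are different verdicts. This is weaker. The joint rule stands under the heading Feasibility outcomes, and the Outcomes section defines feasibility through several components.

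A reader might infer that the Statistical analysis section overrides the joint rule, so that the plan has adopted a retention-only decision. The document gives no order of precedence, so that does not follow. A reader might also take 0.79, or any other single cell of the table, as the likely size of the problem. The protocol gives no expected recruitment rate and says attrition cannot be assessed, so the cells show only that divergence is possible. It would be equally wrong to dismiss the difference in sign because 24 men make it vanish. The aim of at least 12 men per group with full data leaves room to enrol more, although the Statistical analysis section speaks of 24 men assigned.

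It also stands that every component will be measured and reported, so poor recruitment would be visible to a careful reader whatever label is applied.

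**Conclusion.** The point holds as an inconsistency in how the primary decision is stated. The same data can be called feasible under one section and unsuccessful under another.

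The size cannot be fixed from the document. With the 60% target read as enrolled over screened, and under the assumptions listed in the working, the chance of disagreement over recruitment is about 0.05 to 0.86 for true recruitment of 50–70% and true retention of 85–95%. It is small when true recruitment is 70% and considerable at or below 60%. With the target read as a share of the 24 planned men, it is zero if all 24 enrol. A conflict over acceptability depends on neither reading.

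The difference in sign has no effect with exactly 24 enrolled and does matter with 25 or 30.

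This should be corrected before the results are interpreted. It concerns the summary verdict, not the data collected, and may be no more than a drafting slip.

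**What to change.** Replace the retention sentence in the Statistical analysis section with: *Retention meets its criterion if 80% or more of enrolled men complete all three test days; a future RCT will be considered feasible only if all the success criteria listed under Feasibility outcomes are met.*

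Three edits should go with it:
- Use the same inequality in both sections.
- State that the 60% target is enrolled over screened, which is how Feasibility outcomes already defines recruitment.
- Align the Conclusion with this rule. Otherwise a significant result remains a separate trigger for the larger study, in a pilot whose Discussion says it is not powered for group effects.

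No new reporting is needed, since percentages with confidence intervals are already planned for the feasibility outcomes. Acceptability has no numerical measure, so it would still be judged from the reports of subjects and investigators.

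The cost is a few sentences, with no extra participants or data. The downside is that a favourable verdict becomes somewhat harder to reach than on retention alone.

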## Methods/design

### Research hypothesis and study time

We will hypothesize that dietary macronutrient composition has different effects on the metabolic responses and arterial stiffness indices of normal and obese adults. The study protocol will be approved by the Research Ethics Committee of Mashhad University of Medical Sciences, and the pilot study will be completed. The study has been initiated since January 2021 and will continue until March 2021. In total, 24 participants (12 obese men and 12 lean men) will complete the interventions and assessments. Data analysis and reporting of the results will be performed until summer of 2021.

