### Inclusion criteria

The inclusion criteria of the study are as follows: (1) age of 18–40 years; (2) adults with normal weight (body mass index [BMI]: 18.5–23.5 kg/m^2^, body fat percentage: 12–22%, waist circumference < 90 cm), and obese adults (BMI > 27.5 kg/m^2^, body fat percentage > 27%, waist circumference > 95 cm); (3) apparently healthy men; (4) written informed consent to participate; and (5) willingness to undertake the required fasting periods.

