### Measurement tools

#### Anthropometric parameters and body composition

The anthropometric measurements will be performed at the outset of the fasting state by a trained nutritionist. In addition, bodyweight will be measured to the nearest 0.1 kg, with the participants in light clothing. The height of the subjects will be measured using a stadiometer in the standing position to the nearest 0.1 cm. BMI will be defined as the weight (kg) divided by the square of height (m^2^), and waist circumference will be measured at the midline between the iliac crest and lowest ribs to the nearest 0.5 cm. Finally, the body composition of the participants will be determined using bioelectrical impedance analysis (AVIS 333).

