#### Indirect calorimetry

At this stage, the participants will be asked to stay awake and motionless in the supine position, and air samples will be collected using a mask (MetaLyzer 3B-R3 device). Moreover, respiratory gas exchange measurements will be recorded for 20 min in the fasting state, followed by hourly measurements for 6 h after the consumption of the test meals. Furthermore, fasting REE will be measured in a quiet area at room temperature, with the participants in the supine position. The respiratory quotient will also be calculated based on the oxygen consumption and carbon dioxide production, and TEF will be measured as the difference of the postprandial subtracted by the fasting REE. The resting energy expenditure and substrate utilization will also be estimated via indirect calorimetry after resting for 30 min.

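### Lean and obese men are compared by unadjusted tests, so an absolute difference in resting energy expenditure or substrate oxidation partly reflects fat-free mass, which is measured but not used

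*Protocol article*

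**What the plan says.** All places are in the protocol article.

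- **Group tests.** Statistical analysis: "The baseline comparisons between the groups will be performed using the independent samples" t test, or Mann-Whitney U where appropriate. Table 1 lists energy expenditure, resting metabolic rate and substrate oxidation in the Baseline column, so this comparison covers them.
- **Over time.** The same section states that "repeated-measures analysis of variance (ANOVA) will be used to assess the timing effect of the research parameters in various phases of the study". No covariate is named.
- **Measurement.** Indirect calorimetry: "The resting energy expenditure and substrate utilization will also be estimated via indirect calorimetry after resting for 30 min". No units, and no scaling to body size, are given.
- **Body composition.** Table 1 schedules fat and lean mass at Time 0. The method is given under Anthropometric parameters and body composition: "the body composition of the participants will be determined using bioelectrical impedance analysis (AVIS 333". No analysis refers to it.
- **Groups.** Inclusion criteria: lean men have BMI 18.5-23.5 kg/m² and body fat 12-22%. Obese men have BMI above 27.5 kg/m², with "body fat percentage > 27%, waist circumference > 95 cm".
- **Use of the data.** Participants and data collection says the sample should "provide a pooled standard deviation that provides enough precision for the development of a future study".
- **Confounding.** The Discussion says that the design balances confounders and eliminates bias due to subject characteristics.

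**The concern.** The lean-obese contrast in metabolic response is the stated hypothesis and is repeated as an aim in the Discussion. A man with more fat-free mass has a higher absolute REE and oxidises more substrate in absolute terms, even if each kilogram of tissue behaves the same. The entry criteria select groups that tend to differ in this respect. The Discussion's statement on bias can hold for meal contrasts within a man, who serves as his own control. It cannot hold between groups that are formed by BMI, body fat and waist.

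The pilot is about feasibility, but its metabolic data feed three decisions: whether a larger study is designed (the Conclusion ties this to a significant result), which outcome measure that study uses, and the SD that sizes it. A body-size effect could influence the first two, and body-size variance enters the third.

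**Working it through.** **The plan's own figure.** "In total, 24 participants (12 obese men and 12 lean men) will complete the interventions and assessments": 12 + 12 = 24, which is consistent. There is no power calculation to reproduce, since the protocol holds that "it is also not necessary to define and calculate the sample size" and gives no alpha, power, effect size or SD. A pooled SD on 22 degrees of freedom has 95% limits of 0.77 to 1.42 times the estimate.

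**Inputs.** BMI and body-fat limits come from the Inclusion criteria. Everything else is assumed: height 1.75 m, REE slope 20 kcal/day per kg, within-group fat-free-mass (FFM) SD 5 kg, residual REE SD 100 or 150 kcal/day, two-sided alpha 0.05.

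**Step 1: FFM gap.** FFM = BMI × 1.75² × (1 − fat fraction).

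| Man | BMI | Fat | FFM (kg) | Gap from mid-range lean (kg) |
|---|---|---|---|---|
| Lean, mid-range | 21 | 17% | 53.4 | – |
| Obese, entry BMI, higher fat | 27.5 | 32% | 57.3 | 3.9 |
| Obese, entry limit | 27.5 | 27% | 61.5 | 8.1 |
| Obese, assumed | 32 | 32% | 66.6 | 13.3 |

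The groups can overlap: a lean man at BMI 23.5 and 12% fat has 63.3 kg, more than the 61.5 kg at the obese entry limit.

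**Step 2: raw t test on fasting REE, with no size-independent difference.** The mean difference is 20 × gap. The within-group SD is √((20 × 5)² + residual SD²), which is 141 or 180 kcal/day. The noncentrality is (20 × gap / SD) × √6, on 22 degrees of freedom.

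| Gap (kg) | Difference (kcal/day) | Significant, residual SD 100 | Significant, residual SD 150 |
|---|---|---|---|
| 3.9 | 78 | 25% | 17% |
| 8 | 160 | 75% | 55% |
| 13 | 260 | 99% | 92% |

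With wider assumptions (slope 15-25 kcal/day per kg; FFM SD 5 kg with residual SD 100, or 6 kg with 150), the range is 36% to 99.7% for gaps of 8-13 kg and 23% to 59% for 6 kg.

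**Step 3: FFM as covariate (21 degrees of freedom, simulation).** The rejection rate is about 5% at every gap. If measured FFM carries an impedance error with an assumed SD of 3 kg, it is 6-7% at 3.9 kg, 7-11% at 8 kg and 10-16% at 13 kg.

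**Step 4: within-group SD.** FFM explains 100²/141² = 50% or 100²/180² = 31% of the within-group variance. The SD falls by 1 − 100/141 = 29% or 1 − 150/180 = 17%.

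**Step 5: standard error of the group difference.** Unadjusted, with residual SD 150, it is 180 × √(1/6) = 74 kcal/day. Adjusted, the simulated mean is about 81 at a gap of 8 kg and about 105 at 13 kg, because group and FFM become collinear.

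**The case against.** The strongest defence has five parts.

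- **A condensed article.** The statistical section calls itself brief, and covariates and units are often left to an analysis plan. A reader might infer that raw whole-body values will be analysed and that a size difference will be read as a metabolic one. The document does not say so, and per-kilogram reporting is not excluded. What remains is that the article itself names unadjusted tests and asserts that subject-related bias is eliminated.
- **Level versus response.** Every man eats all three meals. In an additive model FFM cancels from his meal contrasts and adds nothing to their SD. The thermic effect of feeding subtracts fasting REE, so the fasting gap drops out of it; its dependence on meal size is a separate matter. This stands and limits the scope. The calculation also covers fasting REE only and gives no figure for oxidation.
- **The gap may be small.** The obese body-fat criterion has no upper limit, so 8 kg is not a lower bound. BMI 27.5 with 35% fat gives 54.7 kg, a gap of only 1.4 kg. This stands, and the range above therefore starts near 4 kg.
- **Adjustment has a price.** Steps 3 and 5 confirm this. Where FFM barely overlaps, the adjusted contrast also relies on extrapolation.
- **The unadjusted difference is a legitimate description** of groups defined by adiposity. This stands, so the adjusted result belongs beside it and should not replace it.

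Finally, these are secondary outcomes of a feasibility pilot that disclaims power for group effects. That lowers the stakes, but does not remove the use of the data for planning.

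**Conclusion.** The concern holds in a limited form. For fasting REE, postprandial energy expenditure and absolute oxidation, an unscaled and unadjusted lean-obese difference cannot by itself show a metabolic difference, and the Discussion's claim about bias is true only within a man. Under the stated assumptions, false significance for fasting REE ranges from about 17% to 99% over gaps of 3.9 to 13 kg, against about 5% adjusted, or 6-16% with impedance error. The slope, SDs, height and alpha are not in the documents, so these figures show the possible size of the effect and do not predict the pilot's result.

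Two stronger readings are not supported. One is that the raw comparison mainly measures lean tissue: eligible men can have small or overlapping FFM, and units are not stated. The other is that adjustment would cut the SD by much more than 17-29%: that would need FFM to explain a larger share of within-group variance than these inputs imply. Respiratory quotient, blood markers, arterial stiffness and within-man meal contrasts are outside this point.

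**What to change.** In Statistical analysis:

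- Report the lean-obese comparison of fasting REE, postprandial energy expenditure and absolute substrate oxidation both unadjusted and with fat-free mass from Time 0 as a covariate, not as a per-kilogram ratio.
- State that an unadjusted difference alone will not be interpreted as a metabolic difference.
- Carry the adjusted SD forward beside the unadjusted one for any between-group sample size. A study sized on the adjusted SD must also allow for the correlation between group and fat-free mass.

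In the Discussion, limit the statement on removed bias to meal contrasts within a man.

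**Cost.** No new data are needed. The adjustment uses one degree of freedom (22 to 21) and can enlarge the standard error when group and fat-free mass are strongly collinear, for example from 74 to about 105 kcal/day at a 13 kg gap with residual SD 150. The report should state this, the extrapolation where fat-free mass barely overlaps, and the residual confounding from impedance error.

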## Abstract

**Background:**

Prior studies have shown that meal composition may affect the metabolic responses and arterial stiffness indices, and these responses may be different in lean and obese adults. The primary objective of this study is to determine the feasibility of conducting a trial to compare the effect of three test meals in lean and obese men. Due to the lack of a comprehensive study that concurrently compares metabolic responses and vascular stiffness indices after receiving three different meals in lean and obese men, this pilot study will be conducted with a three-phase parallel design, aiming to investigate the effects of meal composition on the metabolic parameters and arterial stiffness indices of lean and obese adults.

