**Methods:**

This pilot, a parallel clinical trial will be performed on 24 male adults aged 18–35 years since January 2021 and will continue until March 2021 who are disease-free and selected based on the inclusion and exclusion criteria at Mashhad University of Medical Sciences, Iran. The subjects will complete three interventions at a 1-week interval, including high carbohydrate (70% carbohydrates, 10% protein, 20% fat), high protein (30% protein, 50% carbohydrates, 20% fat), and high-fat meal (50% fat, 40% carbohydrates, 10% protein). Postprandial effects will be assessed within 360 min after each meal, including the energy expenditure component (resting energy expenditure, thermic effects of feeding, respiratory quotient, and substrate oxidation) and arterial stiffness indices (augmentation index and pulse wave velocity). In addition, blood sampling will be performed to measure glucose, insulin, free fatty acids, and lipid profile.

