### Experimental design

The study protocol is based on the SPIRIT guidelines [30]. Figure 1 depicts the diagram of enrollment, intervention, and assessments. Table 1 shows the schedule of enrollment, intervention, and data collection for each participant. This is a parallel clinical trial, and the subjects will consume three different test meals (high-carbohydrate, high-fat, and high-protein) on different days with a 1-week interval between each intervention.

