### Test meals

Three interventions will be implemented in the current research, involving the consumption of high-fat, high-carbohydrate, and high-protein meals as the test meals in a randomized order. On the day of the intervention, the TEE of the subjects will be determined via indirect calorimetry. The test meals will contain 25% TEE for men, and the high-protein meal will consist of bread, cheese, boiled eggs, and skimmed milk (30% protein, 50% carbohydrates, and 20% fat). The high-carbohydrate meal will consist of skimmed milk, white bread, butter, jam, and honey (70% carbohydrates, 20% fat, and 10% protein), and the high-fat meal will contain bread, butter, cream cheese, high-fat milk, and jam (50% fat, 10% protein, and 40% carbohydrates). The subjects will be asked to ingest the test meals within a maximum of 15 min on each test day.

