#### Experimental protocol

The day before each of the three test days, the subjects will prepare their own meals and a standardized daily menu plan, which will consist of 15% protein, 55% carbohydrates, and 30% fat based on their daily energy requirements. The diets will ensure equally filled glycogen stores and similar macronutrient balance in each subject on every test day. The subjects will not be allowed to engage in severe physical activity within 2 days prior to the test days. On the test day, the subjects will arrive at the research center at Imam Reza Hospital at 7 AM with minimum activity (by car/bus) and after fasting from food, drinks (except water), caffeine, and alcohol for the past 12 h.

Before the tests, all the subjects will rest in the supine position for 30 min, lying on a bed in the semirecumbent position until the end of the tests. Initially, all the measurements will be performed in the fasting state and postprandially within 6 h. At the next stage, the participants will randomly receive the test meals and given 15 min to take the meals under the supervision of the researcher until the test meal is completely consumed. Afterwards, the participants will complete a series of tests, including indirect calorimetry, PWV, and pulse wave analysis. In addition, blood samples will be collected within 6 h. All the tests will be carried out in the exact same conditions (e.g., temperature-regulated room and quiet area). Following the test meals, the participants will fast again, refraining from food and drinks (except water) for another 6 h while the testing stage will continue. The testing conditions will be repeated on the next two test days. Figure 2 depicts the schedule of the study days.

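### The trial is labelled parallel but is a three-period crossover, and its only stated model targets change over time, not the meal and meal-by-group comparisons it sets out to make

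*Protocol article*

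**What the plan says.** **Design label.** The abstract states that "this pilot study will be conducted with a three-phase parallel design". The abstract's methods paragraph and the Study setting section also use the word parallel. The Experimental design section puts the label beside the fact that contradicts it: "This is a parallel clinical trial, and the subjects will consume three different test meals".

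**What happens to each man.** The abstract says: "The subjects will complete three interventions at a 1-week interval". The Test meals section describes "high-fat, high-carbohydrate, and high-protein meals as the test meals in a randomized order". Table 1 shows a randomly assigned meal at each of three visits, and the Experimental protocol section says that "the participants will randomly receive the test meals" and that the conditions are repeated on the next two test days.

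**The question.** The hypothesis is that "dietary macronutrient composition has different effects on the metabolic responses and arterial stiffness indices of normal and obese adults". The secondary outcome is to "compare the effect of three test meals on metabolic responses and vascular parameters in lean and obese men for sample size calculation".

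**The analysis.** Apart from descriptive statistics and a normality check, the Statistical analysis section offers two inferential procedures for clinical outcomes. One is a t test or Mann-Whitney test between the groups at baseline. The other is this: "repeated-measures analysis of variance (ANOVA) will be used to assess the timing effect of the research parameters in various phases of the study". It says the data will be used to size the main study. The Conclusion makes the larger study conditional on significance in the measured parameters.

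**The concern.** The factor that is randomised is the meal, and it varies within each man. Lean or obese status is not randomised and varies between men. The question therefore needs two kinds of contrast: between meals within men, and the difference in those contrasts between lean and obese men. The stated model names neither. It names time.

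Two things are at stake. First, an analyst who follows the text would report that outcomes change after eating, and would leave the secondary outcome unanswered. Second, because progression is tied to a significant result, a time effect could satisfy that condition. Some change over six hours after a meal is to be expected whatever the meal, so such a result would say nothing about meal composition.

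The label adds to the problem. The SD needed to size the main trial depends on whether that trial will be parallel or crossover, and the article promises only a pooled SD.

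**Working it through.** **1. The plan's own figure.** 2 groups × 12 men = 24, as stated. No alpha, power, effect size or SD is given, so there is no power calculation to reproduce.

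**2. Structure of the data.** With one summary per man per visit there are 24 × 3 = 72 values and 71 degrees of freedom:

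- between men, 23: group 1, men within group 22;
- within men, 48: meal 2, meal-by-group 2, visit 2, residual 42.

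The hypothesis sits in the meal and meal-by-group lines. The plan's between-group tests are confined to baseline, and its ANOVA is directed at time within visits, which is outside this table.

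**3. Why a time effect cannot stand in for a meal effect.** Take mean changes from fasting in arbitrary units.

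- All three meals give +1: the average time change is +1 and every meal contrast is 0.
- The meals give +1, 0 and −1: the average time change is 0, while the largest meal contrast is 2.

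**4. Illustration by simulation.** Assumptions: 24 men, three meals in random order, four time points, between-subject SD 1, subject-by-meal SD 0.5, residual SD 0.5, 2000 runs. The meal-by-group effect was 0.6 at all time points, with no time effect.

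| Test | Rejections |
|---|---|
| Time | about 4% (its null rate) |
| Meal-by-group, no visit term | about 43% |
| Meal-by-group, with visit term | about 41% |

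The time test stays at its null rate by construction. The table shows what that test is aimed at; it does not estimate power for this trial.

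**5. Why the type of SD matters for planning.** Assume a standardised difference of 0.5 for one pairwise meal contrast, two-sided 5% and 80% power. Then ((1.96 + 0.84)/0.5)² ≈ 31.4.

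- Parallel: 2 × 31.4 = 62.8, so 63 per arm and 189 for three arms.
- Crossover: 2(1 − ρ) × 31.4 men in total, which is 44, 32, 19 and 7 for assumed within-subject correlations ρ of 0.3, 0.5, 0.7 and 0.9.

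**6. A check on the remedy.** A mixed model of all time points with participant as the only random effect would be wrong, because times within a visit share that visit's deviation. With the SDs above and four time points, the meal mean square has null expectation 0.25 + 4 × 0.25 = 1.25. With visit, time and the time interactions with meal and group fitted, the pooled residual is (42 × 1.25 + 198 × 0.25)/240 = 0.425. Here 198 = 24 × 3 × 3 − 18 time-related terms. The ratio is 1.25/0.425 ≈ 2.9. Against a 5% critical value of about 3.03, false rejection is about exp(−3.03/2.94), roughly 35%. The visit-level variation must therefore be modelled.

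**The case against.** The strongest reply is that this is a condensed article, that the analysis paragraph presents itself as a brief summary, and that a fuller analysis plan may exist. The phases may mean the three meal days, with phase as a factor, so that the meal comparison is implied. The word parallel may refer to the two body-weight groups.

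Part of this stands. Covariance structure, visit and sequence terms and the balancing of meal orders are commonly left to an analysis plan, and their absence is not the point here. But the article does name a model, and it gives that model the wrong target. If phase means meal, the sentence still names only timing and has no group factor beyond baseline. If phase means visit, each phase mixes all three meals, because order is randomised, and a phase effect is then mainly a visit-order effect.

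A reader might go further in four ways that the documents do not support.

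- *The meals will be compared as independent groups and within-man precision lost.* Nothing proposes this; repeated-measures ANOVA is a within-subject method.
- *Leaving out visit biases the meal contrasts.* With randomised order it costs precision, not average bias. In the simulation with an assumed drift of 0.5 per visit, type I error stayed near 5%, and rejection of a true meal-by-group effect was about 27% without the visit term and 44% with it.
- *The lack of a no-meal day is an error.* Drift common to the three visits cancels in a meal contrast.
- *The planning variance will not be estimated at all.* The article commits to a pooled SD, and the data allow the needed SDs to be computed.

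**Conclusion.** The point holds. The parallel label contradicts the described conduct, which is a randomised three-period crossover within two non-randomised groups. The only model stated for clinical outcomes does not, as written, test the meal or meal-by-group comparison in the hypothesis and secondary outcome. Together with the progression statement in the Conclusion, it leaves room for a time effect to be read as support for a larger trial.

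Severity is moderate. The feasibility criteria do not depend on this model, and the Discussion states that the pilot is not powered for group effects. The conclusion rests on the text alone. The simulated rejection rates and the sample sizes rest on assumed SDs, effects and correlations, and serve only as illustration.

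**What to change.** 1. Replace the parallel label throughout with a randomised three-period crossover of meals, with lean or obese status as a between-subject factor.
2. For each clinical outcome, name the meal and meal-by-group contrasts as the reported quantities, with 95% confidence intervals. Two routes are sound:
   - one summary per visit, such as the change or area under the curve from that visit's fasting value over the times at which the outcome is sampled, in a mixed model with meal, group, meal-by-group and visit as fixed effects and participant as a random effect; or
   - a model of all time points with the corresponding time terms, which also includes a participant-by-visit random effect or a within-visit correlation.
3. Report the within-subject and between-subject SDs separately for planning the main trial.
4. State in the Conclusion that a change over time after eating is not in itself the result on which the larger study depends.

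The cost is wording and analysis code. The visit term takes 2 degrees of freedom, lowering the within-man residual from 44 to 42. No visit, measurement or participant is added.
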